### Trial objectives

With this trial, we evaluate the efficacy of the online self-help programme “Selfapy” and deduced the following hypotheses. The framework of the trial is superiority. The Becks Depression Inventory - II (BDI-II) [21] thereby serves as the primary outcome measure and assesses the depressive symptomatology.

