#### Main hypotheses

Depressive symptoms (BDI-II scores) will be significantly lower in both study groups following the 3-month “Selfapy” programme compared to the control group.We expect higher depressive symptoms (BDI-II scores) in the unaccompanied group compared to the accompanied group.

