### Sample size

The between-group effect size estimate is based on meta-analytic evidence for the effect size observed in unaccompanied psychological interventions (*d* = 0.28) [16]. Treatment effect sizes in a sample with mild to moderately depressed subjects may be quite low. We conservatively reduced the estimated effect size to *d* = 0.23 [33].

Based on this effect size, a power of 0.80 and an alpha level of 0.05, we need a total of 200 subjects to address our hypotheses. The sample size was further estimated based on an expected drop-out rate of 50%. Drop-out rates in previous studies that used similar interventions ranged between 9% [9, 10] and 50% [34]. Based on this assumption, we would need a total of 400 subjects. The sample size was calculated using G-Power [35]. In addition, a comparison will be drawn between the unaccompanied and the accompanied versions of the online programme. The previously expanded experimental groups are compared to a control group, resulting in a total of three study groups to which the subjects are randomly assigned in a ratio of 2:2:1 (accompanied group: *n* = 160, unaccompanied group: *n* = 160, control group: *n* = 80).

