### Planned statistical analysis

The recorded data of the different measurement times (T1, T2, T3 and T4) for both intervention groups and the control group are analysed. The treatment results of all subjects (pre-post difference) are analysed using intention-to-treat (ITT) analyses.

The primary endpoint is the decrease in depressive symptoms in the BDI-II (Delta BDI-II) between study entrance (T1) and the end of the intervention (T3). A one-way ANOVA (within factor “group”) is performed to analyse the differences in the decrease of depressive symptoms between the intervention groups. A Bonferroni correction for multiple testing is applied to examine the expected group differences. This correction is carried out using the formula *α*/*n* (with alpha level *α* = 0.05 and *n* = number of tests) in order to lower the level of significance, make fewer results significant and thus the number of false-positive results reduce.

In an exploratory analysis, the basic effectiveness of the intervention compared to the control condition is examined (accompanied and unaccompanied group vs. control group) in order to counter the high drop-out rate.

In addition, the mean values including confidence intervals (95%) are recorded. The data are aggregated in the form of mean values and standard deviations. No interim analyses are planned.

To check the data obtained from the measuring instruments for normal distribution, the Kolmogorov-Smirnov test is calculated at the beginning. For this purpose, the mean values and standard deviations of each variable, as well as the Kolmogorov-Smirnov *Z*-value, are calculated, and the asymptotic significance (two-sided) is determined. Values below 0.05 indicate a violation of the normal distribution.

The intermediate measurements are analysed with regard to continuous outcome measures using repeated-measure ANOVAs. Independent *t* tests and *χ*^2^ tests are used to estimate the intergroup differences in sample characteristics prior to treatment.

Missing values in the data are replaced by multiple imputations, as well as “last-observation-carried-forward” (LOCF), “baseline-observation-carried-forward” (BOCF) and a “reference-based multiple imputation” method (“jump-to-reference” approach) to replace the missing values.

Effect size calculations to measure the therapeutic success (before and after the intervention) are carried out by dividing the difference between the respective group mean values by their pooled standard deviation.

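### The trial is sized at an unsplit alpha of 0.05 but its group differences are tested at 0.05/n, so the stated 0.80 is not the power of those tests; Bonferroni is valid here but more conservative than it needs to be

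*Protocol article*

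**What the plan says.** Main hypotheses: BDI-II scores "will be significantly lower in both study groups following the 3-month" programme than in the control group, and the unaccompanied group is expected to score higher than the accompanied group. That makes three pairwise contrasts: accompanied against control, unaccompanied against control, and accompanied against unaccompanied.

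Sample size: "We conservatively reduced the estimated effect size to *d* = 0.23", and with "a power of 0.80 and an alpha level of 0.05, we need a total of 200 subjects to address our hypotheses". No division of alpha is mentioned. The 200 are doubled for 50% drop-out and allocated 2:2:1 (160/160/80).

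Planned statistical analysis: the primary test begins "A one-way ANOVA (within factor" group) and is applied to the BDI-II decrease from T1 to T3. Then "A Bonferroni correction for multiple testing is applied to examine the expected group differences", using alpha/n with alpha = 0.05. The section gives no number for n, does not make a significant ANOVA a condition for the pairwise tests, and describes the ANOVA as comparing the intervention groups. That it covers all three arms is the likely reading, not a stated fact.

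**The concern.** The planning and the analysis use different significance levels for the same questions. A pairwise test judged at 0.0167 has less power than one judged at 0.05, whatever the effect size or sample size, so a reader who takes 0.80 as the chance of confirming a main hypothesis is misled.

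The second part is avoidable loss. With three arms there are rules that control the familywise error at 5% and declare more true differences than plain Bonferroni. What is at stake is the chance of missing a real benefit, particularly on unaccompanied against control and accompanied against unaccompanied, the contrasts that a dismantling design exists to answer.

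**Working it through.** **Inputs.** From the protocol article: alpha 0.05, power 0.80, d = 0.23, 50% drop-out, arms 160/160/80 (80/80/40 after drop-out), three contrasts. Assumed: two-sided tests (sidedness is not stated for the sizing or the group comparisons), equal variances except where noted, and n = 3, with n = 2 as a range.

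**1. The plan's own figure.** The step 200/(1 − 0.5) = 400 reproduces. The 200 does not. For two equal groups, n per group = 2(1.960 + 0.842)²/0.23² ≈ 297, or 594 in total; at 2:1 the total is 669. A three-group ANOVA with 0.23 entered as Cohen's f needs 186, the nearest match at the stated alpha and power. With the two-group conversion f = d/2 = 0.115, the three-group figure is 732. This is a separate and larger issue; the next step does not depend on it.

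**2. Effect of the split on a stated power of 0.80.** Power ≈ Φ(δ − z), where z is the two-sided critical value and δ = 1.960 + 0.842 = 2.802.
- At 0.05: Φ(2.802 − 1.960) = 0.80.
- At 0.05/2: Φ(2.802 − 2.241) = 0.712.
- At 0.05/3: Φ(2.802 − 2.394) = 0.658.

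**3. Why plain Bonferroni is conservative.** With three groups, any two true pairwise null hypotheses imply that all three means are equal, which is what the F-test examines. An F-test at 0.05 followed, only if significant, by pairwise tests at 0.05 is therefore a closed test. Holm compares the smallest p-value with 0.05/3, the next with 0.05/2 and the last with 0.05, stopping at the first failure. It needs no gate and rejects whatever Bonferroni rejects.

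**4. Familywise error by simulation** (pooled-variance tests, 80/80/40 and 160/160/80).
- All means equal: gated rule about 5.0%; Bonferroni/3 and Holm about 4.3%; ungated 0.05 tests about 12%.
- One arm far from the other two: gated rule and Holm about 5.0%; Bonferroni/3 about 1.7%.

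**5. Simulated power, ungated Bonferroni/3 against the alternatives.** Means are in SD units, in the order accompanied/unaccompanied/control.

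| Arms | Means | Contrast | Bonferroni/3 | Holm | Gated |
|---|---|---|---|---|---|
| 160/160/80 | 0.23/0.23/0 | each arm vs control | 23.6% | 25.5% | 29.5% |
| | | both vs control | 13.4% | 16.9% | 23.6% |
| | 0.46/0.23/0 | unaccompanied vs control | 23.5% | 31.9% | 38.4% |
| | | accompanied vs unaccompanied | 36.6% | 44.8% | 52.8% |
| | | accompanied vs control | 83.0% | 83.8% | 86.5% |
| 80/80/40 | 0.23/0.23/0 | each arm vs control | 11.3% | 12.2% | 14.7% |
| | | both vs control | 5.1% | 6.9% | 10.6% |
| | 0.46/0.23/0 | unaccompanied vs control | 11.2% | 14.7% | 20.0% |
| | | accompanied vs unaccompanied | 17.1% | 20.5% | 27.6% |
| | | accompanied vs control | 48.6% | 49.8% | 54.3% |

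The 0.46 is the planning value taken as two equal steps (2 × 0.23). The documents give no effect for accompanied against unaccompanied.

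**The case against.** The best defence is that Bonferroni is valid, prespecified and deliberately cautious, and that the 0.05 in the sizing may belong to the overall ANOVA, since a three-group ANOVA with f = 0.23 comes nearest to 200. On that reading the correction governs only follow-up contrasts. This explains where 0.05 came from, but it does not make 0.80 the power of the pairwise tests, and the main hypotheses are pairwise. Nor is the choice of Bonferroni mere preference: Holm rests on the same assumptions and never rejects less.

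Several stronger readings are tempting and are not supported.
- A reader might infer that the split does nothing because an ANOVA comes first. The protocol does not make the ANOVA a gate, and without one, pairwise tests at 0.05 give about 12% familywise error. As written, the correction is doing necessary work.
- A reader might infer that removing it recovers the full fall from 80% to 66%, or 10 to 17 points. At d = 0.23 the gap between 0.05 and 0.0167 is indeed 10.7 points (80 vs 40: 21.8% to 11.1%) to 17.2 points (160 vs 160: 53.6% to 36.5%, before rounding). But that comparator is the ungated test, which does not control the error. With n = 2 the gap is 7.5 to 11.3 points.
- A reader might take the wording about both study groups as an all-or-nothing claim that needs no correction. It need not be read that way, and the second main hypothesis is a separate claim.

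Two limits on the remedy stand. The gain in the chance of at least one significant contrast is only 1 to 3 points for the gated rule, and nil for Holm, whose first step is Bonferroni's; the benefit is on the further contrasts. And if the control SD is 1.3 times the others (an assumption), error with all means equal is 7.1% for the gated rule against 6.4% for Bonferroni.

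**Conclusion.** The point holds in a limited form. The sizing and the analysis use different alphas, so 0.80 does not describe the tests of the main hypotheses: under n = 3 it corresponds to 66%, under n = 2 to 71%. Bonferroni is valid but gives away power that Holm or a declared gate would keep.

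The recoverable amount depends on the pattern of means. For the gated rule with 160/160/80 it is about 6 points per arm against control and 10 for both together if d = 0.23 in each arm. If the arms are 0.46/0.23/0, it is about 15 and 16 points on the two harder contrasts and 3 to 4 on accompanied against control. With 80/80/40 the corresponding gains are about 3, 5, 9 to 10 and 6 points. Holm gains about 1 to 8 points per contrast with 160/160/80. These figures rest on two-sided tests, three contrasts and equal variances.

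The risk of a false claim is not raised. Nor is the split the main cause of low power: at d = 0.23 even an unsplit 0.05 gives only 22% to 54% per contrast, because 200 does not follow from d = 0.23.

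**What to change.** In Planned statistical analysis, name the three contrasts and replace the Bonferroni sentence with one of two rules.

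- **Holm:** the three pairwise contrasts are tested two-sided with Holm's procedure at a familywise level of 0.05. This is the smaller change and needs no gate.
- **Gate:** the three-arm F-test is carried out at 0.05; only if it is significant is each pairwise contrast tested at two-sided 0.05. The condition must be written out, because without it the error is about 12%. This rule usually gains more.

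If Bonferroni is kept, state n as a number. In Sample size, give the power of each contrast under the rule chosen and, if the first hypothesis is meant as a joint claim, the power of that claim.

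The cost is a reworded correction sentence and a recalculated power statement, with no added patients or data. There are two small downsides. Neither rule comes with simple matching simultaneous confidence intervals, but the plan mentions only 95% intervals for means. The gated rule is also slightly more sensitive to unequal variances under 2:2:1. The article says departures from the protocol will be openly communicated, so the change can be recorded that way; it should be fixed before any unblinded analysis.

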### Outcome measures

#### Primary outcome measure

The primary outcome measure is the change in the self-assessment of depressive symptoms after the completion of the programme using the BDI-II on all assessment points.

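### The first main hypothesis, that each version beats control, is not clearly given a confirmatory test: the only comparison with control that the analysis section names is labelled exploratory

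*Protocol article*

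**What the plan says.** All references are to the protocol article.

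- **Trial objectives and Main hypotheses.** "The framework of the trial is superiority". The first main hypothesis is that BDI-II scores "will be significantly lower in both study groups following the 3-month" programme than in the control group. The second is the contrast between the two versions: "We expect higher depressive symptoms (BDI-II scores) in the unaccompanied group compared to the accompanied group".
- **Primary outcome measure.** The primary outcome is the change in self-rated depression "after the completion of the programme using the BDI-II on all assessment points".
- **Planned statistical analysis.** The primary endpoint is the fall in BDI-II from T1 to T3. A one-way ANOVA is run "to analyse the differences in the decrease of depressive symptoms between the intervention groups". Then: "A Bonferroni correction for multiple testing is applied to examine the expected group differences". The level is α/n, with n the number of tests; neither n nor the tests are listed. The next paragraph reads: "In an exploratory analysis, the basic effectiveness of the intervention compared to the control condition is examined". It names the accompanied and unaccompanied group against control, and gives countering the high drop-out rate as the reason.
- **Sample size.** The calculation starts from an effect for unaccompanied interventions (d = 0.28, reduced to 0.23) and adds accompanied versus unaccompanied as a further comparison. Allocation is 160/160/80, with 50% drop-out expected.

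**The concern.** The hypotheses and the sample-size section both treat control as the main comparator. The analysis section names control in only one test, and gives that test exploratory status. If the text is followed as written, the confirmatory ANOVA addresses the second main hypothesis and nothing confirmatory addresses the first. A later claim that either version beats control could then be challenged as exploratory, or as a choice made after the data were seen.

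Two further points follow from the same paragraph. First, drop-out is not a reason for this comparison. Combining arms would raise the number of observations in the contrast, but would not remove bias from differential or informative attrition. Second, if the exploratory contrast does combine the two versions, it answers a different question from the first hypothesis, which is about each version.

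The open n also matters, because the per-test level depends on which contrasts are in the confirmatory family.

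**Working it through.** **1. Hypotheses against named tests**

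| Contrast | Status in Main hypotheses | Test named in Planned statistical analysis |
|---|---|---|
| Accompanied vs control | Main, first | None by name; control appears only in the exploratory sentence |
| Unaccompanied vs control | Main, first | As above |
| Accompanied vs unaccompanied | Main, second | One-way ANOVA, worded as between the intervention groups |

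The sample-size figure does not settle which test was meant. At d = 0.23, power 0.80 and two-sided α = 0.05, a 1:1 two-sample comparison needs 297 per arm (594 in total), not 200. The nearest between-group result is 186, from a three-group ANOVA with 0.23 read as Cohen's f. That mismatch is a separate matter.

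**2. Time point.** Main hypotheses (after the 3-month programme) and Planned statistical analysis (T1 to T3) agree. Primary outcome measure is the outlier, and its phrase may only describe when BDI-II is collected, since Table 2 lists it at T1 to T4.

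**3. Per-test level with T3 fixed.** α/n is 0.05/2 = 0.025 if only the two comparisons with control are counted, and 0.05/3 = 0.0167 for all three contrasts.

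Effect on unaccompanied vs control at d = 0.23 (two-sided t test, SD = 1):
- 160 vs 80: noncentrality = 0.23/√(1/160 + 1/80) = 0.23/0.137 = 1.68. Power is 0.39 at 0.05, 0.28 at 0.025 and 0.23 at 0.0167.
- 80 vs 40 (50% drop-out): 0.23/√(1/80 + 1/40) = 0.23/0.194 = 1.19. Power is 0.22, 0.14 and 0.11.

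**4. What a pooled contrast could show.** With equal active arms, the pooled effect is the mean of the two effects. Effects of 0.46 and 0 give (0.46 + 0)/2 = 0.23. Effects of 0.23 and 0.23 also give 0.23. In both cases power is about 0.45 (320 vs 80, α = 0.05). The contrast cannot tell one working version from two.

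**5. Choice of multiplicity procedure.** Simulation of three normal groups with common SD and two-sided tests. "Both" below means that each version is significantly better than control. The d of 0.46 is an assumption; 0.23 is the article's figure.

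| d accompanied / unaccompanied | Observed n | Omnibus + Bonferroni (α/3) | Holm | Closed test |
|---|---|---|---|---|
| 0.46 / 0.23 | 160/160/80 | 23% | 32% | 38% |
| 0.46 / 0.23 | 80/80/40 | 10–11% | 14% | 20% |
| 0.23 / 0.23 | 160/160/80 | 13% | 17% | 24% |
| 0.23 / 0.23 | 80/80/40 | 5% | 7% | 10% |

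Family-wise error with no true differences, at 160/160/80, is about 4.2%, 4.4% and 5.0%.

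The closed test is the omnibus F at 0.05, then each pairwise test at 0.05 if F is significant. It is valid for three groups because any two pairwise null hypotheses together imply that all three means are equal. The omnibus test is therefore the only intersection test needed.

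**The case against.** The strongest reply is that a confirmatory test can be read into the text. The analysis section opens by saying that data from both intervention groups and the control group are analysed. Group has three levels under Randomization and blinding. A correction for multiple tests would have little purpose if the ANOVA compared only two arms. The expected group differences are naturally those in Main hypotheses. On this reading the exploratory sentence adds an analysis and demotes nothing. The reading is plausible and may be what the authors meant. It does not remove the point: the article nowhere names accompanied vs control or unaccompanied vs control as a confirmatory test, and it attaches the word exploratory to the one comparison with control that it does name. An unseen analysis plan may list contrasts, but the article has already given the comparison a status that conflicts with its hypotheses.

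Several stronger inferences are tempting, and the document does not support them:
- *The trial definitely has no confirmatory comparison with control.* The three-group reading prevents that conclusion.
- *The exploratory contrast is pooled.* The wording suggests it but does not state it, so the criticism of pooling is conditional.
- *There could be up to nine primary tests (three contrasts at three times).* The analysis section names T1 to T3 as the primary endpoint and sends the intermediate measurements to separate repeated-measures ANOVAs. With T3 fixed, two or three tests is realistic.
- *Bonferroni is an error.* It controls family-wise error; it is only less powerful. Nor is the omnibus gate the cause: Bonferroni without it also gives 23% in the first row of the table.

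It is also fair to say that power is low under every procedure, so the power figures illustrate the choice of procedure and do not measure the ambiguity.

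**Conclusion.** The point holds as a contradiction of status that needs correcting before analysis. The first main hypothesis concerns each version against control, the primary ANOVA is worded around the intervention groups, and the only named comparison with control is exploratory, for a reason that does not address attrition bias. This rests on wording alone and needs no assumption. The time-point discrepancy is minor, because two of the three statements already agree on T3.

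The gain from changing the multiplicity procedure is secondary. Against omnibus plus Bonferroni, the closed test adds about 15 percentage points in the most favourable case shown (38% vs 23%) and about 5 in the least favourable (10% vs 5%). These figures assume normal outcomes with equal variances, three contrasts in the family, two-sided tests (the article does not state sidedness for the primary test) and, for the upper rows, d = 0.46 for the accompanied version. The rows at 80/80/40 treat the expected 50% drop-out as lost observations.

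**What to change.** In Planned statistical analysis:
1. State change in BDI-II from T1 to T3 as the single primary endpoint, and align the Primary outcome measure section with it; results at T2 and T4 are secondary.
2. State that the one-way ANOVA covers all three randomised groups.
3. Name accompanied vs control, unaccompanied vs control, and accompanied vs unaccompanied as the confirmatory contrasts.
4. Fix the multiplicity procedure. Preferably use the closed test (three-group omnibus F at 0.05, then pairwise tests at 0.05), with Holm as the alternative. If Bonferroni is kept, state n = 3.
5. Label any pooled active-versus-control contrast as supportive, and delete the drop-out rationale. Attrition belongs with the missing-data methods already listed.

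The cost is a few sentences in the protocol or analysis plan, dated before database lock. No new data, visits or participants are needed.

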### Assessments

Assessments will be made at four distinct points in time. Baseline (T1, study entrance), 6 weeks after baseline (T2), 3 months after baseline (T3, end of the programme) and 12 weeks after the completion of the programme (T4, follow-up). All other questionnaires are completed by the subjects (self-rating).

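### Repeated-measures ANOVA is a weak choice for the intermediate (and apparently follow-up) scores; a baseline-adjusted mixed model with arm differences at each visit fits the hypotheses better

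*Protocol article*

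**What the plan says.** The section Planned statistical analysis separates two analyses. The primary endpoint, BDI-II change from T1 to T3, has its own one-way ANOVA, which "is performed to analyse the differences in the decrease of depressive symptoms between the intervention groups", with Bonferroni-corrected group differences. For the rest it says: "The intermediate measurements are analysed with regard to continuous outcome measures using repeated-measure ANOVAs". It does not state the time levels, and it names no other method for T4, although it says that data from T1 to T4 are analysed.

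On missing data the same section says "The treatment results of all subjects (pre-post difference) are analysed using intention-to-treat (ITT) analyses" and "Missing values in the data are replaced by multiple imputations, as well as" LOCF, BOCF and a jump-to-reference method. The Sample size section says "The sample size was further estimated based on an expected drop-out rate of 50" per cent.

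The Assessments section says "Assessments will be made at four distinct points in time": baseline, 6 weeks, about 12 weeks and 12 weeks after the programme ends. Table 2 shows that the schedule differs by scale:

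- BDI-II and QIDS-SR16: T1, T2, T3, T4
- BAI, WAI-SR, APOI: T1, T2, T3
- WHOQOL-BREF, HRSD-24: T1, T3, T4
- SWOP-K9, SASS: T1 and T3 only

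The main and secondary hypotheses are stated as comparisons of particular arms: each version with control, and accompanied with unaccompanied.

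**The concern.** The stated method does not match the stated questions. With three arms and four visits, the group-by-time test has (3 − 1) × (4 − 1) = 6 degrees of freedom. A significant result does not say at which visit, or between which arms, a difference lies. The univariate F test also assumes sphericity. Scores taken at 0, 6, 12 and 24 weeks usually correlate less the further apart they are, which breaks that assumption. Finally, entering T1 as one of the outcome levels discards the precision gained by using it as a covariate.

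At stake are the statements about early change, about persistence at T4, and about the continuous secondary scales. The primary conclusion is not at stake.

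**Working it through.** The protocol gives no figure for this analysis, so there is none to reproduce. From the protocol: 160/160/80 subjects, three arms, and the visit times above. Assumed: correlation ρ per 6 weeks of 0.6 to 0.8, decaying as ρ^(gap/6), with equal SDs unless stated otherwise.

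**Sphericity.** With M the covariance matrix of k − 1 orthonormal time contrasts, ε = tr(M)² / [(k − 1) tr(M²)]. Sphericity means ε = 1. For each schedule, 20,000 trials with no effect were simulated and tested at a nominal 5% without correction, for ρ = 0.6, 0.7 and 0.8:

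| Visits (weeks) | ε | Type I error |
|---|---|---|
| 0, 6, 12, 24 | 0.84, 0.79, 0.74 | 6.3%, 6.7%, 7.1% |
| 0, 6, 12 | 0.90, 0.87, 0.85 | 5.4%, 5.6%, 5.9% |
| 0, 12, 24 | 0.96, 0.93, 0.89 | 5.2%, 5.3%, 5.6% |
| 0, 12 | 1 | about 5% |

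With the Greenhouse-Geisser correction the four-visit test returns to 5.1% to 5.2%.

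**Baseline as outcome or as covariate.** In the ANOVA, the interaction contrast of two arms at visit v against T1 is the difference in mean change. Per unit of (1/n₁ + 1/n₂):

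- change score: 2σ²(1 − ρᵥ)
- baseline-adjusted: σ²(1 − ρᵥ²)
- ratio of adjusted to change: (1 + ρᵥ)/2

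At T2, ρᵥ = 0.6 to 0.8, so the ratio is 0.80 to 0.90 and the variance falls by 20% to 10%. At T4, ρᵥ = 0.6⁴ to 0.8⁴ = 0.13 to 0.41, so the ratio is 0.565 to 0.705 and the variance falls by 44% to 30%.

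**Sensitivity to equal SDs.** With a smaller baseline SD σ₀, the change-score variance is σ₀² + σᵥ² − 2ρᵥσ₀σᵥ and the adjusted variance is σᵥ²(1 − ρᵥ²). The difference is (σ₀ − ρᵥσᵥ)², which is never negative. For assumed SDs of 8 at T1, 10 at T2 and 12 at T4:

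- T2, ρᵥ = 0.6: 64 + 100 − 96 = 68 against 64, a 6% reduction
- T2, ρᵥ = 0.8: 64 + 100 − 128 = 36 against 36, no reduction
- T4, ρᵥ = 0.13: 183.1 against 141.6, a 23% reduction
- T4, ρᵥ = 0.41: 129.4 against 119.8, a 7% reduction

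**Missing data.** Trials were simulated at 160/160/80 with SDs 8/10/11/12, correlation 0.7 between adjacent visits, a true T3 difference of −2.5 points, and about 50% drop-out that was missing at random (MAR) with slopes differing by arm. The mean T3 estimates were:

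- unstructured mixed model: −2.56
- multiple imputation: −2.57
- complete cases: −3.74

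The mixed-model and multiple-imputation estimates correlate at 0.99, so on planned multiply imputed data the two routes agree.

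**The case against.** The strongest reply is that this is a condensed article. A sphericity correction, follow-up contrasts and the choice of imputed data set normally belong in an analysis plan, and Greenhouse-Geisser is routine. That stands as far as omissions go. The inflation is modest and easily cured, and it hardly touches most secondary scales. What remains is the choice of method, which the article does state and for which a better one is available.

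A reader might infer that half the sample would be dropped because repeated-measures ANOVA needs complete rows, biasing the result towards the arm that loses its non-improvers. The documents do not support this. The same section plans an intention-to-treat analysis with imputation, and no complete-case analysis is stated. Proper multiple imputation gives essentially the mixed-model answer. Pooling a multi-degree-of-freedom F test across imputations takes a special procedure, but such procedures exist, so nothing shows that the analyst would be driven to LOCF or BOCF.

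A reader might also claim a large gain in power. For d = 0.23 at T3, one simulation gave the omnibus test 30% and a single version-versus-control contrast 53%. That sets an overall test against one contrast at an unsplit 5%. Power of 53% corresponds to a standardised effect of about 1.96 + 0.075 = 2.035. At 0.05/3 (critical value 2.394) power is about 36%, and at 0.05/9 (2.773) about 23%. T3 BDI-II also already has its own test. No power claim is made here.

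Coverage of T4 is an inference, since the sentence says only intermediate measurements.

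**Conclusion.** The point holds as a better choice of method for a non-primary analysis. Run as written, the test is mildly anti-conservative for BDI-II and QIDS-SR16 (about 6% to 7%), slightly so for three-visit scales (about 5% to 6%), and sound in this respect for SWOP-K9 and SASS. It does not deliver the arm-by-arm differences in the hypotheses. It also forgoes precision: 10% to 20% of contrast variance at T2 and 30% to 44% at T4 with equal SDs, falling to 0% to 6% and 7% to 23% with the smaller baseline SD tried above. All these sizes rest on the assumed correlations and SDs.

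On missing data, the mixed model's advantage is that it uses partial records directly under MAR without pooling F tests. It does not give a different estimate from proper multiple imputation. It would be too strong to say that it is superior in every respect, or that the primary result is in doubt.

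**What to change.** Replace the repeated-measures sentence with a mixed model for repeated measures:

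- **Outcome:** post-baseline scores at the visits where Table 2 schedules each scale. State explicitly whether T4 is included.
- **Fixed effects:** arm, visit, arm-by-visit, baseline score and baseline-by-visit, with unstructured covariance.
- **One post-baseline visit (SWOP-K9, SASS):** the model reduces to ANCOVA.
- **Report:** pairwise arm differences with 95% confidence intervals at each visit. Apply the plan's α/n rule, with n stated, to any that are formally tested.
- **Missing data:** keep the listed imputation methods as sensitivity analyses.

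The sample size and the primary T1–T3 one-way ANOVA do not change. The cost is a change of wording and standard software. The output is slightly less familiar to readers than an ANOVA table.
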